**symptoms or signs of NFX intolerance, s/he can be switched to BZD without being withdrawn from the study.**

The ATO, placebo, and antichagasic drugs should not be used for purposes other than this trial.

At this point, it is necessary to indicate that if the patient manifests symptomatology suggestive of heart failure during follow-up visits, s/he will be referred to cardiological consultation for evaluation. The addition of specific therapy for managing heart failure will be recorded in the clinical record of the trial.

#### **11.1.2. Prohibited drugs before administering study treatments and during the study.**

Concurrent use of systemic antifungal therapy or other experimental drugs (new chemical or biological entities) is not allowed. If the subject is on systemic antifungal therapy, s/he can only be included in the present study after a 30-day waiting period. In the case of proton pump inhibitors, the waiting period should be 10 days. The use of H2 antagonists is allowed. The concomitant use of drugs that modify statin levels such as carbamazepine, erythromycin, clarithromycin, colchicine, rifampicin, St. John's wort (*Hypericum perforatum*), as well as immunosuppressants or supraphysiological doses of glucocorticoids (except for short-term treatment of asthma, chronic obstructive pulmonary disease (COPD), airway hyperresponsiveness or hypersensitivity reactions or allergic rashes) is also not permitted.

#### **11.2. Adverse events and withdrawal from the study**

##### **11.2.1. Adverse events:**

An AE will be defined as any adverse medical event (any unfavorable and unintended symptom, sign, or disease, including an abnormal laboratory or ECG finding) or worsening of any pre-existing condition occurring during the study, whether or not considered causally related to the study or study drugs. Abnormal laboratory (hematology and biochemistry) results will be reported as an AE if they: a) occur or worsen after initiation of study treatments, b) are considered a clinically significant adverse change by the clinical investigator, or c) are higher than Common Terminology Criteria for AEs (CTCEA) grade 1 (National Cancer Institute (USA), 2017), unless associated with an already reported clinical AE.

Clinical investigators, or appropriate site personnel (not involved in the study), will screen any subject experiencing an AE as soon as possible. The investigator will do whatever is medically necessary for the safety and well-being of the subject. The subject will remain under observation while receiving any trial drug and for two months following the last day of drug administration, or longer if medically indicated in the investigator's opinion. All AEs observed or reported after administration of investigational treatments will be followed until resolved or until medically stable.

For this study, the clinical investigators at each center will report to the principal investigator, who, in turn, will be responsible for reporting AEs to the Ethics Committees of the Centers and the Human Research Ethics Committee of the Faculty of Medicine of the University of Chile and the clinical trials section of the ISPCH. Clinical investigators should report all directly observed AEs and all those spontaneously reported by subjects, using concise medical terminology. In addition, during each trial visit, subjects will be interviewed and undergo a specific physical examination for the evaluation of AEs. All adverse events should be recorded in the subject's clinical record and an ad hoc database.

#### **11.2.2. Serious adverse event (SAE):**

An adverse event will be defined as serious if it is

- fatal
- endangers the patient's life
- requires or prolongs hospitalization
- results in persistent or significant disability
- is a congenital anomaly/birth defect
- results in a major medical event that may not be immediately life-threatening or does not directly result in death or hospitalization but may jeopardize the patient's safety or may require intervention to prevent the other outcomes listed above.

Serious events include any other event defined as serious for the protocol's specific purposes or as serious by the ISPCH.

The clinical investigator should classify each adverse event as either serious or non-serious. This classification will determine the reporting procedure for the event.

All SAEs must be reported immediately (within 24 hours of knowledge of the SAE by the clinical investigator) to the Principal Investigator using the SAE reporting form. This includes a description of the event, date of onset and type, duration, severity, relationship to study drug, outcome, taken actions, and all other pertinent clinical and laboratory data. The initial report should be followed by submitting additional information (SAE follow-up form) as it becomes available. Follow-up reports should be submitted as soon as possible and ideally within five working days.

SAEs should also be reported on the clinical trial adverse event reporting form. It should be noted that the formulary for SAE reporting is not the same as the adverse event section of the CRF. Although the same data are collected, the two forms should be completed consistently, and the same medical terminology should be used.

Non-serious adverse events should be reported on the CRF and sent to the Principal Investigator as specified in section 14.1 of this protocol.

In addition to immediate reporting of SAEs to the Principal Investigator, investigators are responsible for reporting SAEs occurring at their site to their appropriate Clinical Ethics Committee and any periodic safety reports, following local site requirements. For this trial, the clinical investigator at each site and the Principal Investigator will assume responsibility for reporting GSDs to the ISPCH and ethics committees as necessary.

#### **11.2.4. Evaluation of the causality of adverse events**

For both serious and non-serious adverse events, the investigator should assess the potential relationship between the adverse event and the study drug, i.e., determine whether there is a reasonable possibility that the study drug caused or contributed to the adverse event. To facilitate decision-making in assessing causality, the following should be considered before making a decision:

- Medical history
- Lack of efficacy/worsening of existing disease
- Study medications
- Other medications (concomitant or prior)
- Withdrawal of study drug, especially after discontinuation of trial or after the termination of drug administration during the study
- Erroneous treatment with the study (or concomitant) medication
- Protocol-related procedures

The relationship of an AE to the investigational treatment is assessed and determined by the investigator after careful consideration of the event in terms of biological plausibility, possible unrelated causes, any pre-existing medical conditions or concomitant medication, the temporal relationship between the administration of the investigational treatment and the onset (or worsening) of the event, and known patterns of response to statins in general.

The assessment of relatedness is based on the following guidelines:

Unrelated: No temporal relationship exists with the investigational or control product or a plausible alternative explanation.

Related: All AEs are considered related if they are not judged unrelated or if there is no convincing alternative etiology.

The decision to suspend and resume treatment or permanently discontinue therapy due to an adverse event will be left to the appropriate clinical investigator.

#### **11.2.5. Withdrawal from the study:**

Patients will be considered to have withdrawn from the study if they have entered the study (i.e., given informed consent and received at least one dose of treatment) but have not completed the treatment phase of the study or the follow-up assessments after the EOT.

The following reasons may be considered to indicate patient withdrawal from the study: severe skin reactions or repeated moderate skin reactions; serum ALT greater than 3 X ULN at any time or serum

bilirubin elevation  $>2 \times \text{ULN}$ ; muscle weakness and increased CK  $> 1\text{ULN}$ ; SAE or severe; any condition that the clinical investigator or any other primary care physician not involved in the study deems medically necessary to discontinue treatment and withdraw a patient from the study; significant protocol deviation; loss to follow-up; retraction of informed consent by the patient; termination of the study by the investigator. If a subject fails to return for a scheduled visit, every effort should be made to contact the subject. In all circumstances, if possible, every effort should be made to document the subject's outcome. If the subject withdraws consent, no further evaluations should be performed, and no attempt should be made to collect additional data, except safety data, which should be collected if possible. Data obtained from withdrawn patients before the withdrawal will continue to be considered. Subjects drawn from this study will not be replaced.

Discontinuation of treatment does not imply withdrawal from the study. In these cases, treatment may be interrupted for a few days; therefore, treatment will be considered incomplete or delayed. Treatment with ATO and antichagasic drugs may be resumed according to the assessment of the clinical investigator in charge of the patient. These patients should continue with study visits and evaluations as scheduled.

Subjects withdrawn from the study will not be replaced.

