#### **7.1.4. Treatment of chronic chagasic cardiomyopathy and strategies of improvement:**

In Chile, etiologic treatment of CD is with 5-10 mg/kg/day of nifurtimox (NFX) or 5 mg/kg/day of benznidazole (BZD) for 60 days (MINSAL, 2017). All patients should receive antichagasic treatment without exclusion or delay, except during pregnancy and lactation, although there is recent evidence suggesting that NFX may be safe in these conditions (Moroni et al., 2019). Also, hypersensitivity to trypanocidal drugs excludes its use. Other exclusions are severe renal, hepatic, or cardiac disease, including CCC with structural compromise, alcoholism (Antabuse effect of NFX), and severe megacolon or megaesophagus (MINSAL, 2017).

Treatment of CD is associated with an increased risk of serious adverse events (AEs), with a mean incidence of 16.20% (PAHO, 2018), a situation that may force discontinuation of therapy in up to 48% of patients receiving NFX (Crespillo-Andujar et al., 2018a; Crespillo-Andujar et al., 2018b; Jackson et al., 2020). AEs include weight loss greater than 5-15%, digestive disorders (nausea, vomiting, diarrhea, epigastralgia and dyspepsia, abdominal distension), headaches, irritability, insomnia, mood disorders, memory loss, fever, arthralgias, myalgias, severe or significant skin and mucosal rashes such as Stevens-Johnson syndrome, evidence of thrombocytopenia, pancytopenia or signs of bone marrow depression, elevated transaminases, leukopenia below 2500/mm^3, CNS disorders such as paresis, paralysis or seizures, and behavioral changes, especially in the case of NFX.

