### **12.3. Populations to be analyzed:**

Three populations will be included in the analysis: i) the intention-to-treat (ITT) population comprising all patients randomized by their assigned treatment groups, ii) the per-protocol population comprising all ITT patients without any significant deviation from protocol, and iii) the safety population comprising all patients randomized and having received at least one dose of study treatment.

Descriptive statistics for demographic data and baseline characteristics will be presented for the per-protocol and ITT populations.

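### Protocol section 11.2.5 does not separate stopping treatment from leaving the study, so follow-up to day 360 is unclear for patients who stop permanently

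*Protocol*

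**What the plan says.** Section 11.2.5 makes three statements that bear on who is followed.

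- **Definition.** A patient who has consented and taken at least one dose is withdrawn from the study if they "have not completed the treatment phase of the study or the follow-up assessments after the EOT".
- **List of reasons.** It opens with "The following reasons may be considered to indicate patient withdrawal from the study". It names skin reactions, liver and muscle laboratory findings, and serious or severe events, and goes on to "significant protocol deviation; loss to follow-up; retraction of informed consent by the patient".
- **Later rule.** "Discontinuation of treatment does not imply withdrawal from the study". The next sentence explains it: "In these cases, treatment may be interrupted for a few days; therefore, treatment will be considered incomplete or delayed". Treatment may then be resumed, and these patients keep their visits.

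The same section asks sites to try to establish the outcome whatever the reason for leaving. It keeps data collected before withdrawal, and it expressly ends evaluations only when consent is withdrawn. Withdrawn patients are not replaced.

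Elsewhere, section 11.2.4 lets the clinical investigator stop therapy permanently for an adverse event. Section 11.1.1 allows a switch from nifurtimox to benznidazole for intolerance without study withdrawal. Section 12.3 defines the intention-to-treat set as "comprising all patients randomized by their assigned treatment groups", and section 12.4 makes that set primary.

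**The concern.** Being off drug and being out of the study are different events, and an intention-to-treat analysis needs outcomes from patients who are only the first. The definition joins the two with an *or*, so on its face not completing treatment is enough to be withdrawn. The list then places toxicity findings and protocol deviation beside the two reasons that really do end observation, loss of contact and retracted consent. The rule that would keep patients in follow-up is explained only for short gaps in dosing.

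Four centers could apply this in different ways. Where a patient who has permanently stopped is treated as withdrawn, the 12-month assessment may never be made. Patients who stop because of toxicity or deviation may differ in outcome from those who stay, so the loss could be informative. No later analysis can recover an echocardiogram that was not taken.

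**Working it through.** The point rests on wording, so the provisions are set side by side first.

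| Patient | Definition in 11.2.5 | Later rule in 11.2.5 | Elsewhere |
|---|---|---|---|
| Short interruption, resumes and completes | Not withdrawn | Stays, visits continue | Consistent |
| Nifurtimox intolerance, switches drug | Not withdrawn if treatment is completed | Not addressed | 11.1.1: stays in the study |
| Stops permanently, willing to attend | Withdrawn, if the treatment phase means taking the drug | First sentence keeps the patient; the explanation does not reach this case | 11.2.4 foresees it, without a follow-up rule |
| Meets a listed toxicity or deviation reason | May be deemed withdrawn | Unclear | 12.3 uses significant deviation to define the per-protocol set |
| Retracts consent | Withdrawn, evaluations stop | Not applicable | Consistent |

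Rows three and four have no settled answer. The express exception in section 11.1.1 suggests that stopping a drug might otherwise be taken as withdrawal. Section 11.2.1 requires observation for two months after the last dose, or longer if medically indicated. That is a safety window and does not secure day 360.

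**What is lost (schedule, section 9.6).** The echocardiogram is at screening and day 360 only. Chest X-ray is at screening, day 120 and day 360. The unconditional ECGs are at screening and days 60, 120 and 360. Biomarkers are taken at days 0, 60, 120 and 360. Sections 8.1 and 9.1 place the primary outcome at 12 months and use echocardiography in it. Data from before withdrawal therefore cannot supply the endpoint. Section 12.4 words the primary test in terms of biomarkers, which is a separate matter; the 12-month biomarker sample is also at day 360.

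**Planned loss (section 12.1).** 75 / (1 − 0.25) = 100 per group, so the inflation step reproduces. It allows 25 patients per group to be lost and does not split them by cause. The share due to section 11.2.5 cannot be derived.

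**Illustration of informative loss (assumed inputs).** Let the true response be p = 0.20 in both arms, the placebo rate in section 12.1. Let a fraction d be withdrawn and let r be the response among those withdrawn. The complete-case response is (p − d·r) / (1 − d).

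| Withdrawn, atorvastatin v placebo | r | Complete-case rates | Spurious difference |
|---|---|---|---|
| 25% v 25% | 0 | 0.20/0.75 = 0.267 v 0.267 | 0.000 |
| 30% v 20% | 0 | 0.20/0.70 = 0.286 v 0.20/0.80 = 0.250 | 0.036 |
| 35% v 15% | 0 | 0.20/0.65 = 0.308 v 0.20/0.85 = 0.235 | 0.072 |
| 35% v 15% | 0.10 | 0.165/0.65 = 0.254 v 0.185/0.85 = 0.218 | 0.036 |

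The planned difference is 0.40 − 0.20 = 0.20, so 0.036 is 18% of it and 0.072 is 36%. In this illustration the difference vanishes when withdrawal is equal in the two arms.

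**Timing.** Randomisation is on day 0 and antichagasic treatment comes first in every arm. Withdrawals before atorvastatin or placebo starts should be balanced by arm. Only later ones, such as those for liver or muscle findings, could differ because of the study drug.

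**The case against.** The section is softer than a quick reading suggests. The list is permissive, so meeting a criterion does not by itself remove anyone. Sites are told to seek the outcome in every case, and only retracted consent expressly ends evaluations. The definition also has a harmless reading: section 9.5 uses the treatment phase for a period of scheduled visits, so the definition may mean patients who leave before those visits are done. It would then agree with the later rule. All of this stands, and it limits the point to an ambiguity. It does not remove it, because a best-effort request is not a scheduled assessment and each site must still choose a reading.

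Three stronger conclusions might be inferred, and the protocol supports none of them.

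- **That section 11.2.5 contradicts the intention-to-treat definition.** Section 12.3 keeps every randomised patient in that set and takes deviators out of the per-protocol set only. What may be missing is their outcomes, not their membership.
- **That the background figure in section 7.1.4, "may force discontinuation of therapy in up to 48% of patients receiving NFX", turns into study dropout and discredits the 25% allowance.** It is an upper figure for one drug and concerns stopping therapy. Antichagasic drugs are given in all arms before the blinded phase, and section 11.1.1 permits a switch without withdrawal. It also gives no evidence of differential loss by arm.
- **That worst-case bounds measure this defect.** With 25% missing per arm and observed rates of 0.40 and 0.20, the bounds are 0.75 × 0.20 ± 0.25, or −0.10 to +0.40. They follow from any 25% missingness, including loss made up entirely of retracted consent.

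An analysis plan that is not shown may say how missing outcomes are handled. It cannot supply assessments that were never made.

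**Conclusion.** The concern holds as an ambiguity that should be corrected. The protocol leaves it unclear whether patients who permanently stop treatment, or who meet a listed toxicity or deviation reason, continue to day 360. Reading them as withdrawn would cost 12-month primary-outcome data and weaken the primary analysis.

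The size is not determined by the protocol. The 0.036 and 0.072 are illustrations. They assume different withdrawal by arm, a poorer response among those withdrawn, and an analysis of complete cases; no figure in the protocol shows that withdrawal will differ by arm. Bias is therefore possible but not established.

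**What to change.** Reconcile sections 11.1.1, 11.2.4 and 11.2.5 so that *off treatment* and *off study* are separate statuses.

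1. Remove non-completion of treatment from the definition of study withdrawal.
2. State that every randomised patient, on or off study drug, keeps the scheduled visits and primary-outcome assessments to day 360 unless consent is withdrawn, the patient is lost to follow-up, or the patient dies.
3. Use significant protocol deviation only to define the per-protocol set in section 12.3.
4. Have the investigators reconcile the clinical criteria in the list with the two statuses. No view is given here on those criteria or on when treatment should stop.

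The cost is an amendment to the wording and some extra effort to retain patients who are off drug. The visits are already in the section 9.6 schedule, so no new assessment is added.

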#### **11.2.6. Blind opening procedure**

The blind opening will be performed only in the rare case of a medical emergency or unexpected, severe AEs, when the physician in charge of the patient (and not the investigator responsible for this project) considers that the patient cannot be adequately treated unless the treatment assignment is known. An appropriate blind-opening report should be raised along with completing the AE notification form provided by the ISPCH pharmacovigilance system.

Patients may receive concomitant treatment for medical incidences during the study. All concomitant treatment taken by the patient during the study, from the date of signing the informed consent until the last follow-up visit, will be recorded in the appropriate section of the CRF.

### **12.Data analysis and statistical methods:**

#### **12.1. Sample size:**

A sample size of 75 patients per group is sufficient to achieve a power of 90% at an overall significance level of 5% (2-sided), assuming that the proportion of patients who improve electrocardiographic and echocardiographic parameters, as well as the levels of the cardiac function markers BNP and cTnT in the EOT in the experimental treatment group is 0.40. The proportion in the placebo group is 0.20, with an odds ratio of 2.5. Considering an estimated dropout rate of 25%, 100 patients per group (300 patients in total) would be recruited (Fleiss et al., 2003). The study will be sufficiently powered to provide evidence of the superior efficacy of either statin dose plus antichagasic therapy relative to antichagasic treatment alone.

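### 75 evaluable patients per group gives about 71–77% power for one atorvastatin dose against placebo, not 90%, and the stated odds ratio of 2.5 does not match 0.40 versus 0.20

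*Protocol*

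**What the plan says.** Protocol section 12.1 gives the whole calculation in one paragraph. The headline is "A sample size of 75 patients per group is sufficient to achieve a power of 90% at an overall significance level of 5% (2-sided"). The treated response is given as "in the EOT in the experimental treatment group is 0.40", and for the control arm: "The proportion in the placebo group is 0.20, with an odds ratio of 2.5". A 25% dropout allowance then takes 75 to 100 per group, 300 in all, with a standard textbook on rates and proportions as the source. The paragraph ends with a claim about each dose separately: "The study will be sufficiently powered to provide evidence of the superior efficacy of either statin dose", compared with antichagasic treatment alone.

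Two other places bear on the check. Section 12.4 and the efficacy analysis in the Summary plan a one-sided Fisher's exact test for the primary outcome, with no alpha given there. The Summary also says the two atorvastatin arms will be merged if they do not differ significantly, in which case no multiplicity adjustment is made.

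**The concern.** Everything needed to check the claim is printed in section 12.1: two proportions, a group size, a power, an alpha and its sidedness. For a difference of 0.20 around a mean of 0.30, 75 per group looks too few for 90% power at two-sided 5%. The odds ratio also looks wrong for the two proportions beside it.

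This paragraph is the only numerical justification for the trial's size. If the true power per dose is well below 90%, a null result for one dose will be read as stronger evidence of no effect than it is. The sponsor, ethics committees and later readers would all be working from a miss rate of 10% that the design does not have.

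**Working it through.** **Inputs (Protocol 12.1).** p1 = 0.20 (placebo), p2 = 0.40 (atorvastatin), n = 75 evaluable per group, two-sided alpha 5% (z = 1.960), claimed power 90%, dropout 25%.

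**The step that reproduces.** 75 / (1 − 0.25) = 100 per group.

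**Power by the Fleiss pooled-variance formula.** The mean proportion is 0.30.

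- Standard error under the null: √(2 × 0.30 × 0.70 / 75) = 0.0748
- Standard error under the alternative: √((0.20 × 0.80 + 0.40 × 0.60) / 75) = 0.0730
- Power = Φ[(0.20 − 1.960 × 0.0748) / 0.0730] = Φ(0.730) = **76.7%**

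**Power by Fisher's exact test** (full enumeration of both binomials, two-sided 5%): **71.4%**.

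**Group size for 90% power.**

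- n = [1.960 × √0.42 + 1.282 × √0.40]² / 0.20² = 108.2, so **109** per group
- With continuity correction: (108.2 / 4) × [1 + √(1 + 4 / (108.2 × 0.20))]² = 118.02, so **119** per group
- After 25% dropout: 109 / 0.75 = 145.3, so 146; 119 / 0.75 = 158.7, so 159. The plan recruits 100.

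**Odds ratio.** (0.40 / 0.60) / (0.20 / 0.80) = 2.67. An odds ratio of 2.5 on a control proportion of 0.20 means odds of 0.25 × 2.5 = 0.625, a proportion of 0.625 / 1.625 = 0.385. Power at 75 per group is then 70.4% (Fleiss) or 64.5% (Fisher), so the odds ratio does not explain the 75.

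**Holding the overall level.** Section 12.1 refers to an overall 5% and to either dose, but names no adjustment. If Bonferroni is assumed (2.5% two-sided per dose), per-dose power is 67.1% (Fleiss) or 61.5% (Fisher).

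**Other readings of the text (0.40 versus 0.20).**

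| Reading | Fleiss | Fisher |
|---|---|---|
| One dose, 75 v 75, two-sided 5% (as written) | 76.7% | 71.4% |
| One dose, 75 v 75, one-sided 5% | 85.4% | 80.9% |
| One dose, 100 v 100, two-sided 5% | 87.6% | 84.5% |
| Pooled doses, 150 v 75, two-sided 5% | 87.2% | 86.0% |
| Pooled doses, 150 v 75, one-sided 5% | 93.0% | 91.0% |
| Pooled doses, 200 v 100, two-sided 5% | 95.0% | 94.4% |

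The chance that at least one dose is significant, with two unadjusted two-sided 5% tests at 75 per group, is 89.2% by simulation. The familywise error is then about 9%, so the overall 5% is lost. Holding 5% brings it down to 82.5% (Bonferroni) or 83.8% (Dunnett).

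**Where 75 may have come from.** Two calculations land on 74: one dose, one-sided 5%, 80% power, continuity-corrected (73.5, rounded up); and pooled doses, one-sided 5%, 90% power, continuity-corrected (74 controls). The text does not show which, if either, was used.

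**Effect detectable at 75 per group.** About 90% power at two-sided 5% needs a treated proportion of 0.445 (Fleiss, 90.2%) or 0.46 (Fisher, 90.5%) against 0.20.

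**The case against.** The strongest defence is that 75 and 90% do fit a calculation the protocol partly supports. The primary test is one-sided, and the Summary plans to merge the doses if they do not differ. At 150 versus 75 and one-sided 5%, power is 91.0% by Fisher's test and the continuity-corrected control-group size is 74. On that view the comparison and sidedness were misdescribed, but the number itself is sound. This may be how 75 arose. It does not rescue section 12.1, which says two-sided and claims power for each dose, while pooling depends on what the data show.

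Several further points stand as qualifications:

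- The Fisher figure of 71.4% is two-sided, whereas the planned Fisher test is one-sided. At one-sided 5% the per-dose figure is 80.9%, a miss rate of about 19%. At one-sided 2.5% it is again 71.4%. Sections 12.1 and 12.4 have to be reconciled before one figure can be called the power of the planned test.
- The 62–67% figures rest on Bonferroni, which the protocol does not name.
- The odds-ratio mismatch is small and might be loose rounding.
- Section 12.1 assumes proportions improving at end of treatment, section 9.1 defines the primary outcome as change in cardiomyopathy phase at 12 months, and section 12.4 tests a decrease in biomarkers. The recalculation corrects the stated sum; it is not an estimate of the power for those other endpoints.

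None of these brings a single-dose comparison at 75 per group to 90%.

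**Conclusion.** The concern holds. On the protocol's own inputs, per-dose power at 75 evaluable per group and two-sided 5% is 13 to 19 percentage points below the stated 90%, and the gap widens if the overall 5% is protected across two doses. Even with all 100 per group evaluable, the two-sided figure stays below 90%. The claim of adequate power for either dose is therefore wrong as written, and so is the odds ratio.

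The result assumes independent binomial outcomes, the stated 0.40 and 0.20, and no multiplicity adjustment unless noted. The direction does not depend on the method: unpooled, arcsine, log-odds-ratio and continuity-corrected versions of the two-sided one-dose calculation give 78.2%, 77.3%, 74.9% and 70.8%. This must be fixed, because a stated property of the design is false on its own figures.

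**What to change.** Keep 300 patients and rewrite section 12.1:

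1. Settle whether the primary test is one- or two-sided, and at what alpha, so that sections 12.1 and 12.4 agree.
2. Restate the power at 75 evaluable per arm. At two-sided 5% this is about 71–77% for one dose against placebo and about 86–87% for pooled atorvastatin against placebo. If one-sided 5% is kept, the Fisher figures are 80.9% and 91.0%.
3. Make the effect size consistent: either an odds ratio of 2.67 with 0.40, or a treated proportion of 0.385 with 2.5. With 0.385, restate the power for that assumption (70.4% or 64.5% per dose at two-sided 5%).
4. Delete the claim of adequate power for either dose, unless the primary comparison becomes the pooled arms or the primary analysis becomes a continuous one. If both doses stay in the primary claim, say how the overall 5% is protected and give power at that level.

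The cost is a rewording and a less favourable stated power. No extra patients or visits are needed.
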